### Intervention description {11a}

#### Process of developing the intervention SMS and voice reminder messages

We aimed to use an established framework to identify a theory-informed set of behaviour change principles to guide the development of our reminder messages. We elected to use Dolan and colleagues’ *MINDSPACE* framework [24], developed in conjunction with the Institute for Government. This framework brings together insights from behavioural economics research that can be used to develop brief healthcare interventions (Table 2). The framework has been endorsed by the Behavioural Science and Public Health Network [25], the London School of Economics Behavioral Economics Playbook for behaviour change [10] and the Health Foundation in their guidance on behavioural insights in health care [11].

**Table 2 Tab2:** The ‘MINDSPACE’ framework and application for phone-based reminder messages

Principles	Application
Messenger	People are heavily influenced by the authority and credibility of the person sending the message, so the reminder messages should be signed-off by a trusted official/professional.
Incentives	People are more sensitive to losses than gains, so the reminders should frame non-attendance as a loss.
Norms	People want to fit in and are strongly influenced by the actions of others, so the reminders should signal that attendance is the norm.
Defaults	People tend to ‘go with the flow’ and use pre-set options, so attendance should be the default option in the reminders.
Salience	People are drawn to things that are novel and appear relevant to them, so the reminders should be personalised and stress the novelty of the opportunity.
Priming	Peoples’ decisions are commonly influenced by subconscious cues in their environment. We cannot influence this via phone-message.
Affect	Peoples’ decisions are often based on emotional associations rather than facts, so the reminders should seek to make emotive arguments for attendance.
Commitments	People seek to be consistent with public promises and reciprocate acts, so the reminders should aim to elicit a commitment to attend and stress the social expectation of attendance.
Ego	People act in ways that support the impression of a positive self-image, so the reminders should reinforce the message that attendance is consistent with recipients’ positive self-perceptions.

Whilst SMS and voice messages can include messenger, incentives, norms, defaults, salience, emotional appeals, commitments, and ego, they are less able to ‘prime’ recipients using subconscious cues. In addition to these principles, we also looked to the specific guidance on sending effective phone messages to reduce clinic non-attendance produced by Public Health England in 2020, based on their review of the international literature [26]. Their key messages are summarised below:Messages should be clear, brief and well-formatted, with essential information only.Use line breaks to make the message easier to read.Personalise the text messages to include the recipient’s name if local systems allow.Keep messages to 480 characters (3 standard text messages) in length.Include the date, time, and location of the appointment, as well as any special instructions, and contact phone number (if different to the number the text message is sent from).Write out the day of the week and the month in dates. For example, ‘Monday 23 March’.GP endorsement can encourage people to take screening more seriously.

One researcher (LA) drafted an initial SMS that included all of the eight relevant MINDSPACE behavioural economics elements and adhered to PHE guidance (Fig. 1). We convened a workshop to refine the SMS and develop a pre-recorded voice message with an African economist and representatives from the University of Botswana, and Peek Vision’s Botswana office. Further iterations were made following a robust refinement process (Additional file 1: Appendix 1) that included input from laypeople, and professional translation and back-translation. The final messages are presented in Table 1.

**Fig. 1 Fig1:**
[figure not shown]
First draft SMS reminder. Note: ‘Tebogo’ and ‘[name] are not real names

We will use four arms as outlined below. Each SMS will be sent two times; on the day of referral and on the day before the appointment.

Initially, we will only test arms 1 and 2 (the control and intervention SMS messages). We plan to introduce the voice message arms after 6 weeks. This is because we are interested in introducing new arms at later stages in the screening programme and want to observe how the allocation algorithm handles the introduction of new arms part-way through testing established interventions.Arm 1 (Control): Standard SMS reminder messages.Arm 2: New SMS reminder messages.Arm 3: Standard SMS reminder messages plus the pre-recorded voice reminderArm 4: New SMS reminder messages plus the pre-recorded voice reminder

### Criteria for discontinuing or modifying allocated interventions {11b}

Due to the low-risk nature of the interventions, there will not be any formal option to discontinue or modify the reminder messages.

### Strategies to improve adherence to interventions {11c}

There are no relevant strategies to improve adherence. This is a pragmatic intention-to-treat study, and we will not collect data on whether messages were actually read or listened to by the intended recipients. A potential limitation of this study is that we cannot ensure that the message is actually delivered to- and read by the correct person. To an extent, this is true of all forms of phone-based reminder messages, as it is of paper reminder letters or notes sent by post, or home with children.

### Relevant concomitant care permitted or prohibited during the trial {11d}

No other reminder messages will be sent from the Peek platform during the trial.

### Provisions for post-trial care {30}

As this is a negligible risk trial, no provisions will be made for post-trial care.

### Outcomes {12}

All children who are screened and found to need further assessment and treatment (e.g. refractive services) will be given an appointment, approximately 1 week later, at a specified field ‘triage and treatment’ clinic or at a specialist ophthalmic hospital clinic. The primary outcome is attendance at this pre-specified appointment on the appointment date (yes/no).

The Peek software retains a record of every referred child. When children attend for these appointments, they are checked in using Peek software. This automatically updates their attendance status. Attendance data will be automatically reviewed by an algorithm every 24 h. The great advantage of the Peek-based screening programme is that is a closed data system with complete, unified data records for every person screened, their referral status and their attendance status. No additional data collection activities are required.*Primary outcome*: attendance at clinic on invited date. This is a binary outcome measure (yes/no). We will compare mean outcome rates between arms.*Secondary outcome*: days elapsed between appointment date and attendance. This is because children may miss their appointed day but attend at a later date. We will compare mean number of days elapsed between each arm.*Subgroup analyses*: attendance by age, sex, urban/rural residence, distance to clinic, ethnicity, guardianship, religion, language, household composition, migrant status, parental occupation, housing, assets and income.

### Participant timeline {13}

This automated adaptive trial will run continually for three working months (i.e. pausing during the school holidays when screening does not happen), recruiting participants until sufficient evidence has been gathered to reject the null (by triggering a stopping rule). Enrolment is planned to commence in quarter 3 2022. We intend to start with two SMS arms and add in voice messaging once the trial is underway. This is because we want to observe how the automated allocation system handles the introduction of new arms.

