### Sample size {14}

Approximately 1000 children will be screened every day. Based on previous programmes, we expect approximately 160 of these children to be identified as requiring referral for further assessment and treatment. All of these children’s parents/guardians would receive the standard SMS reminders in a standard programme.

The adaptive allocation method that we are using does not use a pre-specified a sample size. Instead, the study will run until one of two criteria is met:There is a >95% probability that one arm is best.There is a >95% probability that the difference between the arms remaining in the study is <1%.

Depending on the effect of the interventions, one of the stopping criteria might be met after a few days; however, it could also take years before reaching a definitive conclusion. We will set a 3-month limit for this current study due to resource constraints.

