### Recruitment {15}

Community sensitisation is being led by the Ministry of Health and Ministry of Education. This includes TV and radio coverage explaining the Pono Yame screening programme. Our field coordinator will visit each region and work with schools to ensure that they are set up to enrol as many children as possible. Every referred child’s data will be included in the primary analysis. Subgroup analyses will only be permitted for children whose parents have consented for their sociodemographic data to be used for research purposes. This is a separate consenting process led by Peek.

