### Assignment of interventions: blinding

#### Who will be blinded {17a}

Trial participants will not be blinded. Programme implementers will check in participants when they attend clinic using Peek Capture. The software will automatically record the date and the time elapsed since referral. The adaptive algorithm will analyse attendance rates between arms according to pre-defined rules. Screening programme staff and data analysts will be blinded to assignment status. A small team of unblinded human statisticians will monitor the algorithm’s performance. They will double-check the algorithm’s working every 24 h during the trial and will repeat the final analysis comparing each arm. They will have the power to stop the trial, but they will not influence allocation.

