#### Interim analyses {21b}

This is an automated adaptive trial. Our algorithm will review the attendance data every 24 h and perform statistical testing. Two stopping rules will be applied during these daily interim analyses:There is a >95% probability that one arm is best.There is a >95% probability that the difference between the arms remaining in the study is <1%.

If neither of these rules have been satisfied, then the trial (i.e. enrolment) will continue until three months of active screening have elapsed. The Bayesian algorithm will adjust the allocation ratio based on the performance of each arm with respect to the updated posterior probability that each is associated with attendance (Fig. 3).

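### The protocol equates a stopping trigger with rejecting the null while about 800 randomised children have no outcome yet, and does not say which result governs

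*Protocol article*

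**What the plan says.** All of this is in the protocol article.

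- **Participant timeline {13}** describes "recruiting participants until sufficient evidence has been gathered to reject the null (by triggering a stopping rule"). This is the only sentence that says when the null is rejected.
- **Interim analyses {21b}** applies two rules every 24 hours. The first is "There is a >95% probability that one arm is best". If neither is met, "then the trial (i.e. enrolment) will continue until three months of active screening have elapsed".
- **Outcomes {12}**: a referred child "will be given an appointment, approximately 1 week later", and the primary outcome is "attendance at this pre-specified appointment on the appointment date (yes/no").
- **Sample size {14}**: of about 1,000 children screened daily, "we expect approximately 160 of these children to be identified as requiring referral".
- **Recruitment {15}**: "Every referred child’s data will be included in the primary analysis".
- **Who will be blinded {17a}**: unblinded statisticians check the algorithm daily and "will repeat the final analysis comparing each arm". The data cut for that analysis is not given.

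**The concern.** The outcome arrives about a week after randomisation and the rules are checked daily. Whenever a rule triggers, roughly a week of randomised children are still waiting for their appointment. They belong to the primary analysis, but they contributed nothing to the trigger.

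The same comparison can therefore be read at two moments: on the partial data at the stop, and on all referred children about a week later. The two readings differ systematically. A threshold checked daily tends to be crossed on a random high, and later outcomes pull the result back towards the truth. If the trigger is taken as the conclusion, the trial could announce a best message at more than 95% when its complete data give a lower probability, and it would report the more exaggerated of two effect estimates. If the complete data are meant to govern, the timeline sentence is wrong. The article leaves a reader unable to tell which is intended.

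**Working it through.** **Inputs from the protocol**
- 160 referrals per day (Sample size {14}).
- Outcome about 1 week after referral (Outcomes {12}).
- Control attendance about 50% (Background {6a}).
- Daily looks, stop when the probability of being best exceeds 0.95, limit of three months (Interim analyses {21b}).
- Allocation proportional to the probability of being best, and a prior centred at 0.5 with 90% interval 0.44-0.56 (Statistical methods {20a}).

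**Assumptions**
- 5 screening days per week, and about 60 screening days in three months.
- True differences of 0 to 10 percentage points, since the protocol gives none.
- Children whose appointment has not come are left out of the daily update.

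**Step 1. The plan's own figure.** The printed prior, Beta(100,000), lacks a second parameter. Beta(100,100) has 5th and 95th percentiles of 0.442 and 0.558, which reproduces the stated interval. It is used for each arm.

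**Step 2. Children pending at a trigger.** 160 x 5 = 800 (160 x 7 = 1,120 if the lag were 7 screening days).

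**Step 3. Hand check of the mechanism.** Take 1:1 allocation and attendance near 50%. The two priors add 2 x 200 = 400 pseudo-observations. Let I be the observed outcomes plus 400, and let d be the true difference. For a trial that just touches 0.95 (z = 1.645), the complete-data z has

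mean = (1.645 x sqrt(I) + 800d) / sqrt(I + 800), SD = sqrt(800 / (I + 800)).

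- d = 0, median 2,240 observed, I = 2,640: mean 1.44, SD 0.48. The chance of ending below 1.645 is 66%.
- d = 0.05, median 1,280 observed, I = 1,680: mean 2.16, SD 0.57. The chance is 18%.

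Daily batches usually overshoot the threshold, so simulated rates should be somewhat lower than these.

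**Step 4. Simulation of the two-arm phase.** 40,000 runs per effect, 60-day limit, adaptive allocation, 800 pending. At each stop, the declared arm's probability of being best was recomputed with all randomised children.

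| True difference (points) | Rule triggers | Median outcomes in at trigger | At 95% or below with all outcomes, share of stops | Below 90% | Leader changes |
|---|---|---|---|---|---|
| 0 | 36% | 2,240 | 56% | 25% | 0.5% |
| 1 | 48% | 2,560 | 47% | 19% | 0.4% |
| 2 | 73% | 2,560 | 35% | 12% | 0.2% |
| 3 | 91% | 2,080 | 26% | 8% | 0.1% |
| 5 | 99.8% | 1,280 | 12% | 3% | under 0.1% |
| 10 | 100% | 480 | 0.5% | 0.1% | under 0.1% |

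As a share of all trials rather than of stops: 0.362 x 0.561 = 20% at no difference, 0.730 x 0.353 = 26% at 2 points, 0.998 x 0.119 = 12% at 5 points.

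**Step 5. Sensitivity.**
- Two-arm phase limited to 30 days (20,000 runs per effect): 58%, 38%, 27%, 12% and 0.5% at 0, 2, 3, 5 and 10 points.
- Fixed 1:1 allocation, with 640 pending: 56%, 36% and 14% at 0, 2 and 5 points.
- Four arms from day 1, with 640 pending: 27% when one arm is 5 points better and 1.5% when it is 10 points better. With four equal arms only 1.7% of runs stopped, too few for a reliable rate.

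**Step 6. Size of the slip and of the estimate.**
- Among stops that fall back, the median final probability is about 0.89, 0.91 and 0.93 at 0, 2 and 5 points.
- In the 30-day phase the mean estimate is 5.3 points at the trigger and 3.9 with complete data when the truth is 2, and 7.2 against 5.8 when the truth is 5.

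The rule on differences below 1% did not contribute to any of these rates.

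**The case against.** The strongest reply is that the protocol, read as a whole, already does the right thing. The timeline sentence is about how long recruitment lasts. The interim section equates the trial with enrolment, every referred child is in the primary analysis, and a final analysis separate from the daily checks is foreseen. This stands to the extent that a reader who infers that the conclusion is fixed at the trigger goes beyond the text. What remains is that the only sentence defining rejection of the null points to the trigger, and nothing says what follows if the later result differs.

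Second, the 95% threshold is defined only for stopping. For the primary outcome, Outcomes {12} speaks of comparing mean rates between arms. It would therefore be too strong to say that a declared winner fails the trial's own primary analysis, because the protocol sets no 95% criterion there. The simulation shows only that the probability which justified stopping is often not maintained.

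Third, the harm is limited. The slip is usually modest, the leader almost never changes, and from 5 points upwards the problem is small. All of this stands. It does not follow that the trial would often pick the wrong message because of the pending children.

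Fourth, handling of late outcomes is commonly left to an analysis plan. That would answer a complaint of omission, but here the protocol itself states what a trigger means, and states it in a way that sits badly with its own analysis set.

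**Conclusion.** The point holds as an unreconciled conflict within the protocol. The timeline section treats the trigger as the rejection of the null, other sections imply an analysis of all referred children about a week later, and nothing says which governs.

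The disagreement is common when the true difference is about 0-3 points: 56-58% of stops at 0, 35-38% at 2 and 26-27% at 3. It is about 1 in 8 at 5 points and negligible at 10. Small differences matter here because both SMS messages are active reminders and the second stopping rule uses a 1% margin.

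A reader might also infer that using complete data removes the exaggeration of the effect. It does not: 3.9 points for a truth of 2 remains biased by early stopping under daily looks, only less so than 5.3.

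The figures rest on 5 screening days per week, the Beta(100,100) reading of the prior, the assumed differences, and leaving pending children out of the daily update. The section on missing data {20c} sets every child to not attended until updated, and does not say that pending children are left out. Counting them as non-attenders would give far worse results: 94%, 83% and 40% of stops at 95% or below at 0, 2 and 5 points, with the leader reversing in 39%, 35% and 22%. The article does not establish that this is intended, so the conclusion here does not rely on it.

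**What to change.** 1. In Participant timeline {13}, delete the clause that equates triggering a rule with rejecting the null. There and in Interim analyses {21b}, state that a stopping rule ends enrolment only.
2. State that follow-up stays open until the appointment date of the last randomised child has passed, and that the conclusion and the effect estimate come from the posterior on every randomised child at that point.
3. State that an arm is called best only if its probability still exceeds 95% then. Otherwise the final probability is reported with the remark that the threshold was not maintained.

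The cost is a few sentences and about one week's wait after enrolment stops. No extra data collection is needed, since attendance is recorded automatically. The downside is that some trials which trigger the rule will report a probability below 95%. The change does not remove early-stopping bias from the estimate.

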### Objectives {7}

Our objectives are to test a behavioural economics-informed SMS reminder message and a pre-recorded voice message that will be sent to the parents/guardians of school children who have been identified as having a visual impairment and referred to clinic. We hypothesise that these messages will be associated with a higher attendance rate than the current standard SMS reminder that is sent to all referred patients’ parents/guardians.

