### Statistical methods

#### Statistical methods for primary and secondary outcomes {20a}

This study will use Thompson sampling a Bayesian approach to identify the best arm. This is a Bayesian algorithm widely used to learn about arms and optimise decision making [27] Every 24 h, the probability of each arm being the best arm overall will be estimated, using Monte-Carlo simulations to get the posterior probability estimates. As there is no evidence available on how the messages would perform relative to another, a regularising prior of Beta(100,000) (i.e. centred at *p*=0.5 with a 90% credible interval of 0.44–0.56) will be used to avoid overfitting extreme data in the early phase of the trial. It is expected that about 1,000 children will enrol every day, and the observed data will begin to dominate the prior within the first couple of days. Each arm will have a probability of being best between 0 and 100%, and the sum of all two probabilities will equal 100%. These probabilities will be compared to the stopping rules as to whether the trial should stop or continue into the next day. If the trial is to continue, the proportion allocated to each arm for the next day will be updated to be proportional to the estimated probabilities. We will conduct all analyses using the runif and rbeta functions in R (R Foundation for Statistical Computing, Vienna, Austria). Figure 2 illustrates participant flow and operation of the algorithm.

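### Triggering a stopping rule is equated with rejecting the null, but neither rule compares the new messages with the standard SMS; rule 1 stops falsely in about a quarter of null trials and seldom names a voice arm when both work equally

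*Protocol article*

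**What the plan says.** Participant timeline {13} ties the end of recruitment to hypothesis rejection: "recruiting participants until sufficient evidence has been gathered to reject the null (by triggering a stopping rule").

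Interim analyses {21b} and Sample size {14} give two rules. Rule 1: "There is a >95% probability that one arm is best". Rule 2: "There is a >95% probability that the difference between the arms remaining in the study is <1" per cent. The same Interim analyses section sets the frequency: "Our algorithm will review the attendance data every 24 h and perform statistical testing".

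Objectives {7} states the hypothesis as superiority to control: "We hypothesise that these messages will be associated with a higher attendance rate than the current standard SMS reminder".

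Under Intervention description {11a}, arms 1 (standard SMS) and 2 (new SMS) run alone for six weeks. Arms 3 (standard SMS plus voice) and 4 (new SMS plus voice) then enter. Under Statistical methods {20a}, "the proportion allocated to each arm for the next day will be updated to be proportional to the estimated probabilities", that is, to each arm's probability of being best.

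**The concern.** There are two separate problems.

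**The rules do not answer the stated question.** Meeting rule 2 is evidence for little or no difference, the opposite of rejecting a null of no difference. Rule 1 asks which arm ranks first, and the standard SMS can win it. Calling either event rejection of the null invites readers to attach an error rate that the article does not give and that daily checking does not deliver.

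**Rule 1 suits this set of arms poorly.** The four arms form a 2x2 layout of wording by voice. If voice helps and wording adds little, arms 3 and 4 are nearly tied and share the probability of being best, so neither easily passes 95% even when both clearly beat control. Nothing in the article prevents a stop in the first six weeks, before voice has been tried.

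At stake are a false winner in the wording comparison and a real voice effect that the stopping rule does not declare.

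**Working it through.** **Inputs from the article.** 160 referred children per day (Sample size); control attendance about 50% (Background); appointment about one week after referral (Outcomes); voice enters after six weeks (Intervention description); three-month limit (Sample size); daily looks and allocation proportional to the probability of being best.

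**Assumptions.** Six weeks is 30 working days. Three months is 60 working days (65 as a sensitivity). Outcomes become available after 5 working days (0 as a sensitivity). Effects of +5 and +10 points are illustrative.

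**Prior.** The printed parameter cannot be used as it stands, but the interval beside it can: "with a 90% credible interval of 0.44–0.56". Beta(100,100) has SD √(0.25/201) = 0.0353, and 0.5 ± 1.645 × 0.0353 gives 0.442 to 0.558. This reproduces the stated interval, so Beta(100,100) per arm is used.

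**Rule 1 at a single look, two arms.** The rule is met when |m₁ − m₂|/√(s₁² + s₂²) > 1.645, where m and s are the posterior mean and SD. With n children per arm the prior shrinks the statistic by √(n/(n+200)). The null probability is therefore 2[1 − Φ(1.645/√(n/(n+200)))]:
- n = 2,000 (25 matured days × 160 / 2): 8.4%
- n = 2,400 (30 × 160 / 2): 8.7%

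**Rule 1 with daily looks, two arms fixed 1:1, no difference.** 24 looks: 26.5%. 30 looks: 28.6%.

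**Rule 1 under the staged adaptive plan, all arms at 50%.**
- 5-day lag, 60 days: about 25% to 26%. In the 26% run, 24 points fall before voice enters; control is named in 12%, the new SMS in 12% and a voice arm in 2%.
- 65 days: 27%. No lag: 29%.
- Stopping barred until four arms run: 3%. Four arms from day 1: 2%.
- Attendance 43% in all arms: 25% (5-day lag) or 10% (no lag, with the prior centred at 0.5).
- 1,000 per day, the enrolment figure in Statistical methods: 43%.

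**Voice works equally in arms 3 and 4, wording adds nothing.**

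| Voice effect | Lag | Rule 1 fires | A voice arm is named |
|---|---|---|---|
| +5 | 5 days | about 50% | 24% |
| +10 | 5 days | 55% to 56% | 28% to 31% |
| +5 | none | 63% to 65% | 35% |
| +10 | none | 80% to 81% | 53% |

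In the +5, 5-day-lag run, the rule fires in 49%: 25 points are false stops before voice enters and 24 name a voice arm. With stopping barred before voice enters, a voice arm is named in 31% (+5) or 42% (+10).

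**Other patterns.** If only one voice arm is better, by 5 points, it is named in about 68%. If the new SMS and voice each add 5 points, rule 1 fires in 99%, but about 95% of trials stop before voice is tested.

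**Rule 2.** With two arms evenly split over 60 × 160 = 9,600 children, the posterior SD of the difference is √(0.5/(4,800+200)) = 0.010. The probability that the difference lies within ±1 point is then at most 2Φ(1) − 1 = 0.68 (0.70 at 65 days). In that setting rule 2 cannot reach 0.95 within three months.

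**Contrast with control instead.** Allocation was left as planned, trials ran to the limit, and the probability that an arm beats control was checked daily.
- Threshold 0.95: some new arm passes in about 32% of null trials, so changing the contrast alone is not enough.
- Threshold about 0.993: 5% under the global null. A voice arm then beats control in 97% to 98% of trials at +5 and 100% at +10.
- Probability of being best, calibrated to the same 5% (about 0.986 to 0.989): fires in only 13% to 25% at +5 and 22% to 53% at +10.

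**The case against.** A 95% best-arm threshold is a recognised Bayesian choice and is openly stated. Simulated operating characteristics are commonly left to a full protocol or SAP, so their absence from an article is no fault. That stands. The point here is what the article itself fixes: the quantity, the threshold, the frequency of looks and the claim that triggering a rule rejects the null.

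Comparison with control is not confined to rule 1. Outcomes {12} plans to compare rates between arms, and the blinding section has statisticians repeat the final comparison of each arm. That also stands, and it limits the harm. It does not make the Participant timeline sentence correct, and it does not help voice if enrolment has already stopped.

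A reader might infer that a national programme would often adopt a message that is no better. The documents do not support this. About half of the false stops name control, which is current practice; a new message is named in about 14% (26 − 12 points). The article does not say that meeting rule 1 means adoption; Interim analyses describes what continues or stops as enrolment.

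The voice scenario assumes that the new wording adds nothing, which runs against the trial's own premise. This is fair: where one voice arm is distinctly better, the rule does considerably better (about 68%).

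**Conclusion.** The point holds in this form and should be settled before recruitment. The mislabelling is visible from the text alone: neither rule is the comparison with the standard SMS in Objectives. The false-stop rate of rule 1 under the staged plan is about 25% to 29% on the base assumptions (Beta(100,100), 160 per day, 50% attendance, 60 to 65 working days, lag 0 to 5 days), with a range of 10% to 43% when attendance, lag and accrual change. When both voice arms are equally better, a voice arm is named in about 24% to 35% of trials at +5 points and 28% to 53% at +10.

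Three stronger readings are tempting and not supported:
- *Rule 1 fires more often when nothing works than when voice works.* Counted alike from day 1, it fires in about half or more of the trials in which voice works, partly through false stops before voice enters. The low figure is for naming a voice arm.
- *The trial would usually end with no rule met if voice is the active ingredient.* The same counts contradict this.
- *The null rate is high because the rule tests for the best arm.* It comes from uncorrected daily looks in the two-arm phase; with four arms running it is 2% to 3%. Testing for the best arm explains only the poor yield for voice.

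**What to change.** 1. In Participant timeline, remove the reference to rejecting the null and say what each rule shows: rule 1, that one arm (possibly control) ranks first with the stated posterior probability; rule 2, that the remaining arms differ by less than 1%.
2. Keep the probability of being best for allocation only.
3. Base the efficacy conclusion on pre-specified contrasts: each new arm against arm 1, or the wording and voice margins of the 2x2.
4. Set the threshold by simulating the actual design, with its daily looks, staggered entry and outcome lag, and state the resulting false-positive rate. With each arm against control, about 0.993 gives 5% under the global null. A threshold of 0.99 applied to the full set (both margins plus each arm against control) is not enough: it gives 10% one-sided and 17% two-sided.
5. Do not let a trigger in the two-arm phase end the trial before the voice arms have entered.

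**Cost.** Rewording and a short simulation; Trial status says recruitment has not begun. The price is later stopping and fewer early stops for small effects. As a guide from a simpler two-arm, 65-day run, moving from 0.95 to 0.99 shifts the median stop for a 5-point effect from day 13 to day 19. It lowers stopping within 65 days from 99.8% to 95.6% for 5 points (a second check at 0.99 gave 90% to 97%) and from 93% to 61% for 3 points (second check 53% to 65%). Trials that do not stop run to the existing three-month limit and are still analysed.
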